# Management of test subjects.

## Health care

If a subject receives treatment from a physician other than the investigators and subinvestigators of the trial, notify the physician concerned of the subject's participation in the trial by having the subject present a clinical trial participation card, and instruct the subject to contact or enquire with the investigators as necessary.

## Prohibited drugs and drug-free treatment

All concomitant medications (including Seresist^🄬^ (tartirelin hydrate) and Hyltonin Injection^🄬^ (protirelin tartrate hydrate)) are permitted during the study period. However, the dose should be kept as constant as possible for 4 weeks prior to the start of investigational drug administration. For Seresist^🄬^ (tartirelin hydrate), Hyltonin Injection^🄬^ (protilerin tartrate hydrate) and phosphodiesterase 5 inhibitors, initiation or discontinuation during a clinical trial is not permitted and any initiation or discontinuation is treated as a drop-out or discontinuation case. The investigator (sub-investigator) or collaborator should be instructed to promptly inform the investigator (sub-investigator) or collaborator of any changes in concomitant medication.

Rehabilitation started at the time of enrolment in the clinical trial will continue without any change in content. No new rehabilitation will be initiated throughout the duration of the clinical trial.

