| **Drugs prohibited for use in combination with other drugs** | All concomitant medications (including Seresist^🄬^ (tartirelin hydrate) and Hyltonin Injection^🄬^ (protirelin tartrate hydrate)) are permitted during the study period. However, the dose should be constant for 4 weeks prior to the start of investigational drug administration. Celist^🄬^ (Tartirelin hydrate), Hyltonin Injection^🄬^ (Protilerin tartrate hydrate) and phosphodiesterase 5 inhibitors are not permitted to be started or discontinued during a clinical trial and any cases of initiation or discontinuation will be treated as drop-out or discontinuation cases. |
| **Safety assessment.** | Vital signs (temperature, blood pressure, pulse), body weight, adverse events, haematology, blood biochemistry and urinalysis are performed before enrolment, on the first day of treatment and after 4, 8, 16, 24, 32, 40, 48 and 52 weeks of treatment to assess safety. |
| **Efficacy primary endpoint** | SARA 'total' score after 48 weeks  (The primary endpoint is the change from baseline in the SARA 'total' score at the final assessment of the treatment period.) |
| **Efficacy secondary endpoints** | 1. SARA 'total' scores after 4, 8, 16, 24, 32, 40 and 48 weeks 2. SARA 'Walking, standing' score. 3. SARA Scores for each item (except walking and standing scores) 4. Gravity body sway test (total trajectory length for 30 s, rectangular area) 5. Timed Up and Go Test (TUG) (minimum time) 6. Beck Depression Inventory-II (BDI-II) 7. Clinical Global Impression (CGI) 8. Patient Global Impression of Improvement (PGI-I) 9. Short-Form 8 (SF-8) |

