## Exclusion criteria

Patients who fall into any of the following categories should be excluded from coverage.

1) Patients with gait or balance disorders due to medical conditions other than spinocerebellar degeneration (stroke, brain tumor, head injury, multiple sclerosis, hypothyroidism, alcoholic ataxia, joint disease, others).

2) Patients with arginase deficiency (which exacerbates argininemia), patients with lysinuric protein intolerance who have a greater degree of inhibition of arginine absorption (which causes diarrhea with the use of arginine preparations).

3) Patients with dementia (MMSE<=23), mental illness (psychosis, manic-depressive illness, depression without treatment [Beck Depression Inventory score>=21]), or a history of suicidal attempt.

4) Patients with complications that are considered inappropriate for participation in the study, such as serious heart disease, liver disease, kidney disease, or hematologic disease.

5) Pregnant or possibly pregnant patients and breastfeeding patients.

6) Patients who are unable to consent to use effective contraceptive methods during the study participation period.

7) Patients who took oral preparations that were judged by the principal investigator or the subinvestigator to be supplements containing algin U or L-arginine as the main ingredient within 30 days prior to the date of informed consent.

8) Patients who participated in another clinical trial within 6 months before the date of obtaining informed consent.

9) Patients who are considered inappropriate to participate in the study by the principal investigator or the subinvestigator.

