### Basis for setting exclusion criteria.

1), 7), 8) To eliminate any influence on the assessment of efficacy or safety.

2), 3), 4) To ensure the safety of subjects and to eliminate any influence on the assessment of safety.

5), 6) To ensure the safety of the subjects and their foetuses and newborns.

9) To avoid incorporating persons who are not suitable for this clinical trial.

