### Basis for setting doses.

The active drug is covered by insurance for congenital urea cycle disorders and lysinuric protein intolerance as ARGI-U^®^ combination granules, with doses indicated up to 0.5 g/kg/day (0.384 g/kg/day as L-arginine).

On the other hand, in pharmacological studies, efficacy was observed in SCA1 knock-in mice with oral administration of 6% L-arginine hydrochloride (Fig. 8.3.3a), and in subsequent studies to determine the effective concentration range, an improvement trend was observed with administration of 4% and 6% L-arginine (Fig. 8.3.3b). Furthermore, a partial efficacy was also observed with 2% L-arginine hydrochloride (Fig. 8.3.3c).

Figure 8.3.3a. therapeutic effect of oral administration of L-arginine hydrochloride (6%) on SCA1 knock-in mice.

[figure not shown]

SCA1 knock-in or wild-type mice were orally administered L-arginine hydrochloride (6%) or water from 3 weeks of age and locomotor function was assessed in the rotarod test. The results showed that oral administration of L-arginine hydrochloride (6%) significantly improved locomotor disturbance in SCA1 knock-in mice.

Fig. 8.3.3b. Therapeutic effect of oral administration of L-arginine hydrochloride (6%) on SCA1 knock-in mice.

[figure not shown]

SCA1 knock-in or wild-type mice were orally administered L-arginine hydrochloride (2-6%) or water from the age of 3 weeks and their locomotor function was assessed in a rotarod test (4 weeks). The results showed that oral administration of L-arginine hydrochloride (4-6%) tended to improve locomotor deficits in SCA1 knock-in mice.

Fig. 8.3.3c. Effect of treatment with oral L-arginine hydrochloride (2%) from post-onset SCA1 knock-in mice.

[figure not shown]

L-arginine hydrochloride (2%) or water was orally administered to SCA1 knock-in mice from 5 weeks after the onset of locomotor disturbance and locomotor function was assessed in the rotarod test. The results showed that oral administration of L-arginine hydrochloride (2%) from after the onset of SCA1 knock-in mice also resulted in significant improvement of locomotor disturbance.

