Human equivalent doses based on FDA criteria for L-arginine doses to mice correspond to approximately 0.27 g/kg/day (2%), 0.54 g/kg/day (4%) and 0.80 g/kg/day (6%) (as ARGI-U^®^ combination granules, approximately 0.35, 0.7 and 1.0 g/kg/day respectively). At a dose of 0.5 g/kg/day of ARGI-U^®^ combination granules, a test subject weighing 60 kg would take 30 g/day of formulated granules (10 g at a time as three divided doses). Based on the results of animal studies, higher doses (0.7~1.0 g/kg/day) may be expected to have a higher effect.

In terms of safety, the drug is a water-soluble amino acid preparation and is considered to be virtually harmless to the human body. Furthermore, for congenital urea cycle disorders and lysinuric protein intolerance, the dose of ARGI-U ^®^ combination granules is 0.5 g/kg/day and may be increased or decreased as appropriate. However, there are no data on the safety of long-term use of L-arginine 0.8 g/kg/day (40 g at 50 kg), and when a single dose of L-arginine 0.8 g/kg/day equivalent to 50 kg was taken in volunteers in a pilot study, diarrhoea symptoms occurred at a high frequency. As this is a long-term study, it is important to ensure safety and tolerability. Therefore, a dose of 0.384 g/kg/day of L-arginine (0.5 g/kg/day as ARGI-U^®^ Combination Granules), which is assumed to be effective and has been well tolerated in other diseases, was set.

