## Criteria for discontinuation of a clinical trial per subject.

The investigator or sub-investigator sh discontinue the subject's clinical trial in the following cases

1. If the subject withdraws consent to participate in the clinical trial

If consent is withdrawn for the use of all data, a consent withdrawal form should in principle be used, except in cases where it is difficult to come to the hospital. If only some of the survey items are withdrawn, a consent withdrawal form is not required and this should be recorded in the source documents.

1. When it is deemed difficult to continue the administration of the investigational drug to the subject concerned due to adverse events, etc.
2. Treatment that is deemed to have a significant impact on the outcome of the trial, such as the administration of surgical treatment during the trial period.
3. If a female subject becomes pregnant during the trial (if the male subject's partner becomes pregnant, the trial can continue)
4. If it is found after registration that the inclusion/exclusion criteria are violated.
5. If the subject is unable to continue the clinical trial for non-medical reasons (e.g. hospital transfer, relocation, etc.)
6. Other cases where the investigator or sub-investigator decides that it is difficult to continue the trial.

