### Analysis of plasma drug concentrations.

If necessary, plasma drug concentrations are analysed for data where plasma arginine concentrations are detected.

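### Section 9.2 leaves ARGI-U permitted and L-arginine supplements unrestricted after consent, although exclusion criterion 7 bars both for the 30 days before it

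*Protocol*

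**What the plan says.** Section 9.2 states that concomitant medications of every kind "are permitted during the study period. However, the dose should be kept as constant as possible for 4 weeks prior to the start" (the start meant is the first dose). It then forbids starting or stopping three groups on trial (tartirelin, protirelin and phosphodiesterase 5 inhibitors) and treats any such case as a drop-out or discontinuation. New rehabilitation is also barred. The synopsis has the same rule in slightly firmer words, that these medications "are permitted during the study period. However, the dose should be constant for 4 weeks prior to the start" of dosing, with the same three groups. Neither place names L-arginine.

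Exclusion criterion 7 in section 5.2 does name it. It excludes patients who took oral preparations judged to be "supplements containing algin U or L-arginine as the main ingredient within 30 days prior to the date of informed consent". Read with the rest of the protocol, the first product name is ARGI-U, the marketed granules used as the active drug. Section 5.2.1 gives the purpose: "1), 7), 8) To eliminate any influence on the assessment of efficacy or safety".

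**The concern.** The reason given for criterion 7 holds at least as strongly for the 48 weeks of treatment as for the 30 days before consent. The protocol nevertheless lets the bar lapse at consent, and section 9.2 then gives a general permission that covers ARGI-U.

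A placebo patient could therefore start the test ingredient without breaching any stated drug rule. It would not be an eligibility breach either, because criterion 7 looks only backwards from consent. If L-arginine slows progression, such use makes the placebo arm look more like the active arm and biases the primary comparison of SARA change towards no difference. If L-arginine does nothing, efficacy is unaffected.

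Criterion 7 also shows that the sponsor thought some candidates might be users. With 20 patients per arm, set as a feasibility minimum (section 8.2.1), each contaminated patient is one twentieth of the control arm.

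**Working it through.** The protocol gives no figure on this point, so there is none to reproduce. The check has three parts.

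**1. The rules by period**

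| Period | ARGI-U | L-arginine supplements |
|---|---|---|
| 30 days before consent | Barred (criterion 7) | Barred (criterion 7) |
| Consent to Week 52 | Permitted as a concomitant medication (9.2, synopsis) | Not mentioned: neither permitted nor barred |

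The dosing rules (8.3.2), discontinuation criteria (10.2) and case-handling rules (14.2) contain no express bar on non-study L-arginine.

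**2. Size of the dilution**

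Inputs from the protocol: 20 placebo patients; natural SARA change in SCA6 of 1.3 to 1.6 points per year (8.3.4); trial dose 0.384 g/kg/day as L-arginine (8.3.3). Assumptions: use from Week 0, the same treatment effect in all patients, and a user who gets a share f of the full-dose effect.

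- Effect over 48 weeks if the drug halts progression completely: 48/52 × 1.3 = 1.20 and 48/52 × 1.6 = 1.48 points.
- With k users, the difference becomes (1 − k × f/20) × effect.
- k = 0: no loss.
- k = 1, f = 0.25: loss 0.25/20 = 1.25%, that is 0.0125 × 1.20 = 0.015 to 0.0125 × 1.48 = 0.018 points.
- k = 1, f = 1: loss 1/20 = 5%, that is 0.05 × 1.20 = 0.060 to 0.05 × 1.48 = 0.074 points. This is a ceiling per user: f = 1 implies an outside intake like the trial dose, 0.384 × 60 = 23 g/day at 60 kg, for the whole 48 weeks.

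The loss grows in proportion to the number of users.

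**3. Would the existing section 9.2 sanction repair it?**

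Section 9.2 treats a start or stop of its listed drugs as a drop-out or discontinuation. Section 14.2 then analyses the case with the change at the last visit. Take linear progression with natural 48-week change D, complete arrest at full dose, and a placebo patient who starts L-arginine at week t.

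- Followed to Week 48: recorded progression falls short by f × (1 − t/48) × D.
- Discontinued at week t and analysed at the last visit: it falls short by (1 − t/48) × D.
- Ratio of the second to the first: 1/f, so equal at f = 1 and four times as large at f = 0.25.

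Example with t = 24, f = 0.25, D = 1.20: 0.25 × 0.5 × 1.20 = 0.15 points if followed, against 0.5 × 1.20 = 0.60 points if discontinued. If the full-dose effect is less than complete arrest, the comparison favours follow-up still more. Extending the existing sanction to L-arginine would therefore do at least as much damage as the use it penalises.

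**The case against.** Partial controls exist. Section 8.5.2 has concomitant drugs recorded with dose, duration and reason, and section 9.2 asks for prompt reporting of changes. Section 10.2 has the investigator discontinue a subject for "Treatment that is deemed to have a significant impact on the outcome of the trial, such as the administration of surgical treatment". These make use visible and leave room to act. But section 10.2 is a site judgement with surgery as its example, and it sits beside an express permission. Plasma arginine is sampled, yet section 14.3.4 says only "If necessary, plasma drug concentrations are analysed for data where plasma arginine concentrations are detected", so it is no fixed safeguard. The consent document must list matters for subjects to observe (6.3). That text is not shown and may contain an instruction on L-arginine; even so, the protocol itself would need to agree with it.

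Three stronger readings are tempting, and the documents do not support them.

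- A reader might infer that the protocol permits L-arginine in every form. That holds for ARGI-U as a drug. For supplements, which section 9.2 does not mention, the protocol is silent rather than permissive.
- A reader might infer serious dilution. Criterion 7 has already removed recent users, so mainly new starters remain, and nothing in the documents suggests that they would take about 23 g/day.
- A reader might infer an overdose risk in the active arm. ARGI-U is covered "with doses indicated up to 0.5 g/kg/day (0.384 g/kg/day as L-arginine"), and 0.384 + 0.384 = 0.768 g/kg/day is close to the level of which section 8.3.3 says "there are no data on the safety of long-term use of L-arginine 0.8 g/kg/day". Reaching it would take full-dose ARGI-U on top of trial drug, about 60 g of granules a day at 60 kg. ARGI-U is insured for congenital urea cycle disorders and lysinuric protein intolerance, and criterion 2 excludes arginase deficiency and a group with lysinuric protein intolerance. A treating physician would also see the trial participation card (9.1). This is too remote to count in the size of the problem.

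**Conclusion.** The gap is real and limited. The protocol protects against outside L-arginine before consent and then drops that protection: ARGI-U is expressly permitted on trial, and supplements are left unrestricted. The direction of any bias is known: towards no difference if L-arginine works, and none if it does not.

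Its size cannot be fixed from the documents, which give neither a user count nor a supplement dose. It is zero with no users. Per placebo user from Week 0 it is 1.25% of the difference at an assumed quarter of the full effect, with 5% as an unlikely ceiling. It is probably small overall, on the assumption that supplement doses fall well below the trial dose. This is a point to consider, not one that puts the trial's conclusions in doubt. It is worth acting on because the correction is cheap.

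**What to change.** In section 9.2 and the synopsis, state that ARGI-U and oral preparations with L-arginine as the main ingredient, other than the investigational drug, are not permitted from informed consent to Week 52. Use the terms of criterion 7, so that one definition covers the time before and after consent.

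Do not attach the existing drop-out rule. Record any use as a protocol deviation with product, dose and dates. Keep the patient in follow-up to Week 48 and in the full analysis set with the observed Week 48 value. Exclude major breaches only from the per-protocol set.

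The cost is one clause in each place and one line in the instructions to subjects. No visit or test is added, since concomitant drugs are already recorded. Patients forgo L-arginine products during the trial; section 3.2.5 reports no clinical trials of L-arginine in this disease, so no established treatment is withheld. Some dilution from breaches stays in the full analysis set, but on the working above it is no larger than what early truncation would cause.

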## Follow-up after completion or interruption of the clinical trial (when necessary)

Undertake follow-up as necessary on adverse events observed during the trial period, in accordance with the instructions of the investigator or sub-investigator.

# Ensuring the safety of test subjects

## Ensuring the safety of subjects

The investigators and sub-investigators should comply with the following basic requirements to ensure the safety of the subjects

(i) The investigators and sub-investigators should comply with this protocol.

(ii) The investigators and sub-investigators should endeavour to detect adverse events at an early stage, and if they consider that an adverse event has occurred and treatment is necessary for the subject, they should inform the subject and provide appropriate medical treatment. (iii) The investigators and sub-investigators should discontinue the clinical trial for the subject concerned depending on the severity of the adverse event in accordance with section 10.2 of this protocol.

(iii) If the investigators and subinvestigators receive new safety or adverse effect information related to the investigational drug that may affect subject participation, they will promptly communicate this information to the subject in accordance with section 11.6 of this protocol.

## Criteria for discontinuation of a clinical trial per subject.

The investigator or sub-investigator sh discontinue the subject's clinical trial in the following cases

1. If the subject withdraws consent to participate in the clinical trial

If consent is withdrawn for the use of all data, a consent withdrawal form should in principle be used, except in cases where it is difficult to come to the hospital. If only some of the survey items are withdrawn, a consent withdrawal form is not required and this should be recorded in the source documents.

1. When it is deemed difficult to continue the administration of the investigational drug to the subject concerned due to adverse events, etc.
2. Treatment that is deemed to have a significant impact on the outcome of the trial, such as the administration of surgical treatment during the trial period.
3. If a female subject becomes pregnant during the trial (if the male subject's partner becomes pregnant, the trial can continue)
4. If it is found after registration that the inclusion/exclusion criteria are violated.
5. If the subject is unable to continue the clinical trial for non-medical reasons (e.g. hospital transfer, relocation, etc.)
6. Other cases where the investigator or sub-investigator decides that it is difficult to continue the trial.

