### Efficacy primary endpoint

Change from baseline in SARA 'total' score at 48 weeks post-treatment.

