| AJA030 PK blood sampling ^#4^ |  |  |  | ○ | ○ |  |  | 〇 |  |  | ○ | ○ | <○> |
| Identification of adverse events^#5^ |  |  |  |  |  |  |  |  |  |  |  |  |  |
| Concomitant medications and therapies |  |  |  |  |  |  |  |  |  |  |  |  |  |

#1: Performed in female subjects of childbearing potential (if pregnancy test is performed with blood, draw approximately 2 mL more blood separately).

#2: If data from pre-registration testing is within one week of the start date of administration, the data may be adopted.

#3: Only cases from Niigata University Medical and Dental Hospital should be conducted.

#4: At the visit where the blood level measurement sample is collected, the subject must be instructed to allow at least 6 hours between taking the investigational drug and collecting the sample. At the morning visit, do not take study medication before or after breakfast. At the afternoon visit, do not take the investigational drug before or after lunch. Any investigational medicines skipped for blood concentration measurement should be submitted to the investigator or collaborator as leftover medicines at the time of the visit. There is no need to take them together at the next oral dose.

#5: Adverse event assessments at the start date of dosing are carried out after the administration of theinvestigational drug.

#6: Weeks 12, 20, 28, 36 and 44 will be telephoned by the site's clinical trial staff to check status and to confirm internal medication status. Tolerance is ±7 days.

<○>: If the investigational drug is discontinued during the investigational drug administration period, it will be carried out as far as possible.

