At the visit to collect the blood sample, the subject should be instructed to allow at least 6 hours between taking the investigational drug and collecting the sample. The site staff should confirm with the subject the date and time of the most recent dose of investigational drug prior to collection of the blood sample. Record the date and time of collection of the blood concentration specimen. The date on the case report form should be clearly recorded (e.g. DD MM YYYYY) and the time of collection should be recorded to the minute (HH:MM, 24-hour format).

1. **Identification of adverse events**

1) Observation period: starting date, 4, 8, 16, 24, 32, 40, 48 and 52 weeks, and at discontinuation

2) Observations: name of adverse event, date of onset, severity, severity, causal relationship to investigational, treatment, outcome and date of outcome

1. **Check concomitant medications and concomitant therapies**

1) Observation period: pre-enrolment, at start of treatment, 4, 8, 16, 24, 32, 40, 48 and 52 weeks, and at discontinuation

2) Observations: concomitant medications

Record the drug name (generic name), route of administration, dose, duration of administration and reason for concomitant use.
 Concomitant therapy

Record the name of the treatment, date and reason for implementation.

　(* when cancelled) should be carried out as far as possible, and the absence does not constitute a deviation from the plan.

If the data from the pre-registration test is within one week of the start date of administration, the data from the pre-registration test may be adopted as the data for the start date of the investigational drug administration.

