## Procedure for discontinuation of a clinical trial per subject.

The investigator decides whether the subject can continue the trial and, if not possible, follows the procedure for discontinuation.

- - - 1. The investigator or subinvestigator should promptly explain the discontinuation of the clinical trial to

the subject concerned and the surrogate if any, and take necessary measures such as provision of

appropriate medical care and guidance on health management.

2) Information on subjects collected in accordance with the study protocol before discontinuation of the study will be analyzed in accordance with section 13 of the study protocol.

3)　For subjects who have received an investigational drug, check safety after discontinuation of the investigational drug.

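### Patients who stop the drug, or start or stop a listed drug, leave the trial with no week-48 SARA, and their last score stands in for it

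*Protocol*

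**What the plan says.** **Exit from the trial.** Protocol section 10.2 lists grounds on which the investigator ends the subject's participation. One is "When it is deemed difficult to continue the administration of the investigational drug to the subject concerned due to adverse events, etc". Another is an eligibility violation found after registration. Section 9.2 adds tartirelin, protirelin and phosphodiesterase 5 inhibitors: "any initiation or discontinuation is treated as a drop-out or discontinuation case".

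**SARA after exit.** The schedule in section 8.5.1 has a single discontinuation column, and its footnote on SARA reads "If the investigational drug is discontinued during the investigational drug administration period, it will be carried out as far as possible". The same footnote in the synopsis table speaks of the study being discontinued, so the two events are used interchangeably. Section 8.5.2 says of these assessments that they "should be carried out as far as possible, and the absence does not constitute a deviation from the plan". The later step in section 10.3 is "For subjects who have received an investigational drug, check safety after discontinuation of the investigational drug". No section asks for SARA at week 48 after discontinuation.

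**Analysis.** Section 10.3 states: "Information on subjects collected in accordance with the study protocol before discontinuation of the study will be analyzed". Section 14.2 includes discontinued and drop-out cases with the change from pre-medication to the last visit. Section 8.4.2 defines the primary endpoint as "Change from baseline in SARA 'total' score at 48 weeks post-treatment", and section 14.3.3 specifies an analysis of covariance of that change. The synopsis adds a different wording: "The primary endpoint is the change from baseline in the SARA 'total' score at the final assessment of the treatment period".

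**The concern.** The drug is meant to slow a disease that worsens steadily. A score taken at week 8 or 16 and entered as if it were the week-48 result leaves out most of the worsening that the trial is built to detect, so early exit looks like slower progression. If exits differ between arms, for example because of gastrointestinal tolerability, the difference enters the primary comparison as an apparent drug effect. With 20 patients per arm, a few unequal exits are enough to matter.

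The statistical analysis plan cannot repair this alone. It can choose another method for the missing week-48 scores, but it cannot produce visits that the protocol does not schedule.

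**Working it through.** The protocol states no power, standard deviation, effect size or drop-out rate (section 8.2.1 sets 40 patients on feasibility), so there is no planned figure to reproduce. The check gives the size of the distortion.

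**Inputs from the protocol**
- Expected progression in SCA6: 1.3 to 1.6 SARA points per year (section 8.3.4).
- Endpoint at week 48 (sections 8.4.2, 14.3.3); last-visit rule (section 14.2).
- 20 patients per arm (section 8.2); one-sided α of 0.025 (section 14.3.3).

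**Assumptions, not in the protocol**
- Linear progression at the same rate in both arms (no drug effect).
- Stoppers: 4 active and 1 placebo, or 8 and 2, all with a last SARA at week 16.

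**Step 1. Expected change by week 48:** rate × 48/52.
1.3 × 48/52 = 1.20; 1.6 × 48/52 = 1.48.

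**Step 2. Value carried forward from week 16:** rate × 16/52.
1.3 × 16/52 = 0.40; 1.6 × 16/52 = 0.49.

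**Step 3. Understatement per stopper:** rate × (48 − 16)/52.
1.3 × 32/52 = 0.80; 1.6 × 32/52 = 0.98.

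**Step 4. Bias in the arm difference:** understatement × difference in stopping fractions.

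| Stoppers, active vs placebo | Difference in fractions | Bias towards active (points) | Share of 48-week progression |
|---|---|---|---|
| equal numbers and timing | 0 | about 0 | 0% |
| 4 vs 1 | 3/20 = 0.15 | 0.12 to 0.15 | 0.15 × 32/48 = 10% |
| 8 vs 2 | 6/20 = 0.30 | 0.24 to 0.30 | 0.30 × 32/48 = 20% |

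The sign reverses if placebo patients leave earlier or more often.

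**Step 5. False-positive rate, as an illustration.** The planned analysis of covariance was simulated with no drug effect (8,000 runs per setting). Further assumptions: standard deviation of the 48-week change 1.5 or 2.5, split equally between slope and measurement variance; exits at random at week 4, 8, 16 or 24, unrelated to the patient's own slope. One-sided type I error was 0.036 to 0.046 with 4 vs 1 stoppers and 0.054 to 0.093 with 8 vs 2. With every patient observed at week 48 it was 0.024 to 0.028, which is the nominal 0.025 within simulation error.

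**The case against.** **Discontinued patients are not dropped.** A reader might infer that the primary comparison covers only those who tolerated treatment and stayed in. The protocol does not support that. Section 14.2 enters discontinued patients with their last-visit change, the full analysis set in section 14.1.2 excludes only undosed patients and those with no efficacy measurement, and the synopsis wording of the endpoint fits this. Nor does section 10.3 say that only data from before discontinuation will be used. The fault is carry-forward of an early value, not selection of completers. SARA is also taken at seven visits up to week 48, so a missed exit assessment seldom leaves a patient without a score.

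**The per-patient loss is not a group effect.** It is tempting to set the 0.80 to 0.98 points of one week-16 stopper against the mean effect of a drug that halves progression (half of 1.20 to 1.48, or 0.60 to 0.74). The two are not comparable: the per-patient figure must first be multiplied by the difference in stopping fractions.

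**Stopping may be rare and balanced.** Adverse reactions occurred in 12.5% of 40 pre-approval patients and in 8.1% of 222 post-marketing patients (section 3.2.5), and each main expected event was below 5% (section 11.3.1). The frequent diarrhoea in section 8.3.3 followed 0.8 g/kg/day of L-arginine, about twice the trial's 0.384. These are reaction rates in other diseases, not stopping rates here. They make the 8 vs 2 case look pessimistic, but they do not show that the arms will be balanced. Not every exit is informative either: an eligibility violation found late need not relate to tolerability or worsening.

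**A different question may be intended.** This is a pilot, and a score at the end of treatment answers an on-treatment question, whereas follow-up off drug dilutes a true effect. That is a fair choice to debate. But sections 8.4.2 and 14.3.3 define the endpoint at week 48 and test it at one-sided 0.025, and the last-visit value does not measure that endpoint. The secondary mixed model uses repeated visits, but it is not the primary analysis and has no scores after exit.

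**Conclusion.** The point holds. Discontinuing the drug, a late-found eligibility violation, or starting or stopping a listed drug ends the subject's trial. One optional SARA follows, and no week-48 SARA is requested. The last-visit change then replaces the week-48 change that defines the primary endpoint.

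In a disease expected to worsen by 1.20 to 1.48 points over 48 weeks, this favours the arm that stops earlier or more often: by 0.12 to 0.15 points at 4 vs 1 stoppers at week 16, by 0.24 to 0.30 at 8 vs 2, and by about zero if stopping is equal and the drug has no effect. The stopping counts and the simulation's standard deviations are assumptions, and the protocol does not show which arm would lose more patients. Direction and size are therefore uncertain, but the gap in data collection is not. It should be corrected, and correcting it is cheap.

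**What to change.** 1. **Sections 10.2 and 10.3:** separate stopping the investigational drug from withdrawing from the study. Leave all reasons for stopping the drug, and all concomitant-drug rules, as they are.
2. **Sections 8.5.1, 8.5.2 and 10.3:** patients who meet a discontinuation criterion but do not withdraw consent keep the scheduled SARA visits, at minimum week 48. Make the discontinuation SARA required unless consent is withdrawn.
3. **Sections 9.2 and 14.2:** record starting or stopping a listed drug as an event, and use the observed week-48 score in the primary full-analysis-set comparison in place of the last-visit value. The last-visit analysis may remain as a sensitivity analysis. Align the synopsis wording of the endpoint with section 8.4.2.

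**Cost:** a short amendment and a few already-scheduled visits for patients off drug, some of whom will decline. Scores collected off drug will dilute a true on-drug effect to some degree. Patients who withdraw consent will still be missing at week 48.
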